### Randomisation and blinding

The allocation to the surgical technique to be used will be placed in an opaque, sealed envelope by a study investigator. Once sealed, the envelopes will be randomly mixed before being numbered consecutively. No pre-stratification is required. The Principal Investigator will be blind to this process throughout.

Once the patient has arrived in the anaesthetic room of the operating theatre, the randomisation envelopes will be drawn in consecutive numerical fashion by the Principal Investigator and a member of the theatre team. This will determine which surgical technique the patient will receive. A master file containing a log of those involved in randomisation will be used for verification purposes.

Patients will be blinded to their study group at the time of entering theatre. It is not possible to blind the operating surgeon/Principal Investigator. No “sham” incisions will be used to blind the patients undergoing surgery to the intervention allocated. Unblinding will be permissible should patients present with a postoperative complication that requires repeat surgical intervention.

### Statistical analysis and trial end points

The intended data analysis will be on an intention-to-treat and per-protocol basis to demonstrate non-inferiority. This will allow bias between the treatment arms to be minimised, and demonstrate the efficacy of the intervention itself. Data analysis will be performed by one of the study investigators using SPSS v22 for Mac (IBM Inc., Armonk NY, USA), and will be verified by the local unit R&D department. Data will be tested for normality using the Shapiro Wilk test. Appropriate parametric and non-parametric tests will used accordingly.

Primary outcome measures will be compared between groups at set postoperative time points of 3, 6, 12, 18 and 24 months. Additionally, outcomes at these time points will be compared to preoperative baseline i.e. the analysis metric will be the change from preoperative baseline. This will allow calculation of change in patient-reported outcome scores at the set time points and the change in these reported scores over the study timeframe.

For primary and secondary outcome scores, the mean ± SD, median and range will be given for continuous data. For the secondary outcomes, the frequency of complications and all-reason revision will be recorded as a percentage and analysed by chi square analysis. For all tests, a *p* value <0.05 will be considered significant.

End points will be completion of the study timeframe (2 years), or further dislocation/all reason revision surgery. The trial will only be stopped should information become available that indicates that it is unethical to use synthetic grafts.

We propose to test non-inferiority using the intention-to-treat analysis set. No crossover of treatment arms will be allowed to occur as part of the protocol. Therefore, the study shall include all participants, as randomised. Patients will be reviewed at each specified time point as previously outlined. A single imputation model with last value carried over (LVCO) will be employed should patients drop out or be lost to follow up. The trial is designed to accommodate a 60% dropout rate, and still maintain a suitable sample size for meaningful statistical analysis.

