### Outcomes

The primary outcome will be to determine the patient-reported outcome score using the validated Kujala score [32]. This is a validated scoring system designed specifically for patellar instability [32]. Scores will be collated preoperatively, and at the pre-defined postoperative time points of 3, 6, 12, 18 and 24 months. This will be identical for both autologous and synthetic reconstruction techniques. Specifically, we will report the change in the Kujala score at these set time points and analyse the data for differences between surgical techniques to determine if one appears to be superior. This will demonstrate the efficacy of the treatments under investigation, and allow a meaningful statistical comparison between the treatment arms.

Additional secondary outcomes scores will also be reported. These will be collected at the same time points as the primary outcome score, preoperatively and then postoperatively at 3, 6, 12, 18 and 24 months. The outcome scores will include the Tegner Activity Level Scale [33], Lysholm Knee Score [34], the Banff Patellar Instability Index (BPII) [35] and the anterior cruciate ligament (ACL) Quality of Life Score [36]. These scores have been previously validated and are reliable in assessing ligamentous injuries of the knee and are commonly reported in studies of ligamentous reconstruction.

Other secondary outcomes will include the incidence of complications and all-reason revision surgery. Those patients lost to follow up will have their data included up to this point to allow for analysis at the set postoperative time points. The aim is to have data on medium-term outcomes at 2 years for all participants.

At each study-review time point, participants will be questioned about adverse events attributable to undergoing surgical reconstruction of the MPFL that they have experienced since their previous review. This will include graft rupture/failure, synovitis, persistent instability and reoperation/revision surgery.

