### Sample size

Sample size was calculated using a web-based calculator (www.openepi.com). Results from a previous study using an ACL autologous reconstruction technique were used to define the control group [21]. The authors reported a postoperative increase in the Kujala score from 56.7 ± 17.7 (2×SD) to 86.8 ± 14.4 (2×SD). Success rates of isolated MPFL reconstruction are good, with patients reporting good or excellent outcomes of 87–96% [3, 21].

The minimally clinically important difference is defined as half of a standard deviation according to the method utilized by Norman et al*.* [37]. Using the result from Panni et al., we determined that σ = 7.2 in the treatment cohort, and therefore assumed a difference in 10 points would be clinically detectable and relevant.

Using a 1:1 enrolment ratio in a non-inferiority trial design, with beta of 0.2 and alpha of 0.05, a total of 30 patients will be required – 15 in each treatment arm. A Cohen’s *d* value of 1.01 with an effect size of 0.58 means that any significant difference attributable to the treatment received should be found using this sample size. Using the results of a previously published study [21], a minimum sample size of 10 patients – 5 in each arm – will be required in order to detect a clinical difference in the treatment groups.

Therefore, the aim is to recruit 15 patients in each group into this study, which allows for an attrition rate of up to 60% in each group. This will still allow meaningful statistical analysis to be performed. This is relevant due to the young age of the study population, which therefore has potential to be affected by population migration and loss to follow up. Clinical follow up will occur postoperatively at intervals of 3, 6, 12, 18 and 24 months.

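### The trial is called non-inferiority, but no margin or confidence bound is designated, so the plan has no rule by which non-inferiority can be shown

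*Protocol article*

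**What the plan says.** The Sample size section sets the framework: "Using a 1:1 enrolment ratio in a non-inferiority trial design, with beta of 0.2 and alpha of 0.05". It concludes that "a total of 30 patients will be required – 15 in each treatment arm". The same section takes autologous reconstruction as the control, so synthetic is the arm to be shown non-inferior. It defines the important difference as half an SD, states an SD of 7.2, and then takes 10 points as the relevant difference. It does not call either figure a margin. It adds that "a minimum sample size of 10 patients – 5 in each arm – will be required in order to detect a clinical difference", which is the language of a difference test.

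Statistical analysis and trial end points opens with "The intended data analysis will be on an intention-to-treat and per-protocol basis to demonstrate non-inferiority" and later says "We propose to test non-inferiority using the intention-to-treat analysis set". It plans parametric or non-parametric tests, chosen after a normality check, and compares the primary outcome between groups at five postoperative time points, using change from baseline. None of the five is named as the point for the non-inferiority test. The only criterion, for all tests, is a p "value <0.05 will be considered significant".

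The Outcomes section states another aim: to "analyse the data for differences between surgical techniques to determine if one appears to be superior".

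**The concern.** Non-inferiority is a claim that any deficit is smaller than a stated amount. It needs that amount, and a bound on the estimated difference that excludes it. The article supplies neither. A p-value against zero difference answers another question: a significant result can show that the grafts differ, while a non-significant result shows only that the trial did not detect a difference.

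At stake is the trial's main conclusion. If the margin is chosen after the results are known, the choice can decide the verdict. If no margin is ever chosen, the non-inferiority claim has no basis. The two statements of the analysis set add to this, because the text does not say what follows if the ITT and per-protocol results disagree.

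**Working it through.** **Inputs.** From Sample size: 15 per arm, alpha 0.05 (sidedness not given), power 80%, SD 7.2, a 10-point relevant difference, a half-SD rule (0.5 × 7.2 = 3.6 points) and d = 1.01. An SD of 14.4 is also tried. The article prints 14.4 as twice the SD, so using it as one SD is an assumption that departs from the article.

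**Step 1: reproduce the stated size.** Per arm, n = 2 × [(1.960 + 0.842)/d]².
- d = 1.01 gives 15.39, so 16 per arm or 32 in total, within two patients of the stated 30.
- d = 10/7.2 = 1.389 gives 8.14, so 9 per arm or 18 in total.

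The stated size therefore follows from d = 1.01, not from 10 points with SD 7.2. With 10 points, d = 1.01 would need an SD of 10/1.01 = 9.9, which the article does not give. The same formula serves a two-sided difference test and a one-sided 0.025 non-inferiority test with a margin of d SDs and no true difference. Reproducing 30 thus does not reveal which was meant, and it does not identify 10 points as the margin.

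**Step 2: what a non-significant difference test would mean.** Take 15 per arm, a two-sided t-test at 0.05, 28 degrees of freedom and critical value 2.048. The non-centrality is λ = (deficit/SD) × √(15/2), and P(non-significant) is the probability that a non-central t with that λ lies between −2.048 and 2.048.

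| True deficit of synthetic | SD | Deficit/SD | λ | P(non-significant) |
|---|---|---|---|---|
| 3.6 (half-SD rule) | 7.2 | 0.500 | 1.37 | 74% |
| 10 | 7.2 | 1.389 | 3.80 | 4% |
| 10 | 14.4 (assumption) | 0.694 | 1.90 | 55% |

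A CI rule with M = 10 would wrongly declare non-inferiority in 2.5% of trials when the true deficit is 10, whatever the SD.

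**Step 3: how much the margin decides.** The half-width of the 95% CI at 15 per arm is 2.048 × SD × √(2/15): 5.4 points at SD 7.2 and 10.8 at SD 14.4. With no true difference, the power of the CI rule is P(non-central t > 2.048) with λ = (M/SD) × √(15/2).

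| M | SD | Power at 15 per arm | Per arm for 80% power (normal formula) |
|---|---|---|---|
| 10 | 7.2 | 96% | 9 |
| 10 | 14.4 (assumption) | 45% | 33 |
| 3.6 | 7.2 | 26% | 63 |

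The two figures in the Sample size section thus lead to opposite prospects. With M = 10 and SD 7.2, a true deficit of 3.6 points would still be declared non-inferior in 65% of trials. That is acceptable only if 3.6 points is not regarded as important, and the half-SD rule says that it is.

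The SD of the change score, which is the stated analysis metric, is not given, so all these results carry the score SD over to it.

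**The case against.** The strongest reply is that the gap is one of labelling. Ten points is the only difference in Kujala points that the article adopts, and it appears just before the non-inferiority sizing. A non-inferiority test also yields a p-value, against a shifted null, and the article never says that its null is zero. The exact CI method may be left to an analysis plan. The two statements on the analysis set can be read as analysing both sets and testing on ITT. With the article's own 10 points and SD 7.2, a difference test at 15 per arm would miss the deficit in only 4% of trials.

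Much of this stands. Ten points is the natural candidate, the test is under-specified rather than shown to be wrong, and the conflict over analysis sets is the lesser part of the point. But a margin is an input to a non-inferiority sample size, and this article reports its other inputs in detail. The 10 points neither gives the stated N with SD 7.2 nor agrees with the half-SD rule beside it, and the Outcomes section points to superiority.

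A reader might infer more than the document supports:
- **That p>0.05 will be reported as non-inferiority.** The article does not say so; it gives no other rule.
- **That the test will run on six patients per arm, because 60% attrition is accepted.** The plan carries last values forward and includes everyone as randomised, so 15 per arm stay in the ITT analysis.
- **That carrying values forward pulls the arms together.** With unequal dropout the bias can go either way, and nothing in the article settles it.
- **That a non-significant result is the default whenever synthetic is importantly worse.** That fails for a 10-point deficit at SD 7.2.

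**Conclusion.** The point holds. The article commits to non-inferiority in two sections but designates no margin, no confidence bound and no single time point, and it describes a superiority question elsewhere. A non-significant difference test cannot fill the gap. At 15 per arm it would occur in 74% of trials with a true deficit of half an SD, but in only 4% with a true deficit of 10 points at SD 7.2. The 55% figure for 10 points depends on assuming an SD of 14.4 against the article's stated 7.2. All three assume normal scores, equal SDs, 15 analysed per arm and a two-sided 0.05 test. The lack of a rule does not depend on these assumptions; only the size of the risk does. Because the main conclusion cannot be reached by the plan as written, this must be settled before outcomes are compared.

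**What to change.** In Statistical analysis and trial end points, state one rule. Synthetic is non-inferior if the lower limit of the two-sided 95% CI for synthetic minus autograft in the Kujala score lies above −M. The measure is change from baseline, preferably adjusted for baseline, at one named time point such as 24 months. Require the ITT and per-protocol results to agree, and say so wherever the analysis set is described.

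Fix M, with a justification, before any outcome data by arm are seen. Ten points is the natural candidate, but it must be reconciled with the half-SD rule. Restate power at 15 per arm for the chosen M: about 96% for M = 10 at SD 7.2, 45% for M = 10 if the SD is 14.4, and 26% for M = 3.6 at SD 7.2. State that p>0.05 is not evidence of non-inferiority. Align the Outcomes section so that superiority is tested only after non-inferiority is shown.

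Stating the rule takes a protocol and registry amendment and no new data. The cost is that a non-inferiority claim becomes harder to reach. A half-SD margin would leave the trial clearly underpowered, since 80% power would need 63 per arm. If no margin can be justified, withdraw the non-inferiority wording and report the difference with its confidence interval.

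### Neither between-group Kujala comparison is stated to adjust for the baseline score already collected, and a Shapiro-Wilk test picks the method: a precision loss of perhaps a third to a half for the change score, under stated assumptions

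*Protocol article*

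**What the plan says.** Under Statistical analysis and trial end points, the Protocol article describes two comparisons. The first is of scores at each visit: "Primary outcome measures will be compared between groups at set postoperative time points of 3, 6, 12, 18 and 24 months". The second, introduced as an addition, is relative to baseline: "the analysis metric will be the change from preoperative baseline". The Outcomes section describes the primary outcome in the second way: "we will report the change in the Kujala score at these set time points and analyse the data for differences between surgical techniques".

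The method depends on a pre-test: "Data will be tested for normality using the Shapiro Wilk test", followed by "Appropriate parametric and non-parametric tests will used accordingly". No test is named and no covariate is mentioned.

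The baseline score is available for every patient: "Scores will be collated preoperatively, and at the pre-defined postoperative time points of 3, 6, 12, 18 and 24 months". Randomisation is simple ("No pre-stratification is required") and the target is 30 patients, 15 per arm. The only spreads given are in the Sample size section, from a cited autograft study whose Kujala score rose "from 56.7 ± 17.7 (2×SD) to 86.8 ± 14.4 (2×SD". The protocol therefore plans with σ = 7.2, the postoperative value, and treats 10 points as the relevant difference. It gives neither a pre/post correlation nor an SD of change.

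**The concern.** A raw change score subtracts the whole of the baseline, noise included. That is efficient only when the regression of follow-up on baseline has a slope near 1. In the cited data the baseline spread exceeds the follow-up spread, so the slope is below 1 at any correlation under 17.7/14.4 = 1.23, that is, always. Raw change then over-corrects. A comparison of follow-up scores alone errs the other way and ignores baseline altogether. Adjusting for baseline estimates the slope and is more precise than either whenever the correlation is material.

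The trial is small and unstratified, so a chance baseline difference of several points is quite possible. In a change-score comparison such a difference carries into the treatment contrast through regression to the mean.

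The Shapiro-Wilk step adds a separate weakness. A non-inferiority judgement needs one prespecified estimate in Kujala points with its interval. Under the plan, a normality test with little power at this size decides which kind of result is produced.

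**Working it through.** **Inputs.** Spreads 17.7 (pre) and 14.4 (post), labelled 2×SD, so SDs 8.85 and 7.2; 15 per arm; difference 10 points (all Sample size section). Correlation ρ = 0.3, 0.5, 0.7 is assumed. One-sided 0.025 is assumed, since the protocol gives alpha 0.05 without sidedness. Ten points is used as the margin because it is the only candidate the protocol names.

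**The plan's own figure.** By the normal approximation, n per arm = 2(1.96 + 0.84)²/d² ≈ 15.7/d².
- d = 1.01: 15.4, so 16 per arm, close to the stated 15. The implied SD is 10/1.01 = 9.9.
- 10 points with SD 7.2: d = 1.39, so 9 per arm.

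The stated 15 thus fits d = 1.01, not the stated 10 points and 7.2. In neither case is an SD of change derived.

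**Variances per patient.**
- Change: s_pre² + s_post² − 2ρ·s_pre·s_post
- ANCOVA: s_post²(1 − ρ²)
- Follow-up alone: s_post²

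With 8.85 and 7.2, s_pre² = 78.32, s_post² = 51.84 and 2·s_pre·s_post = 127.44.

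| ρ | Var(change) | Var(ANCOVA) | Ratio | Loss, change | Loss, follow-up alone (ρ²) |
|---|---|---|---|---|---|
| 0.3 | 91.93 | 47.17 | 0.513 | 48.7% | 9% |
| 0.5 | 66.44 | 38.88 | 0.585 | 41.5% | 25% |
| 0.7 | 40.95 | 26.44 | 0.646 | 35.4% | 49% |

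The ratio is the same whether or not 17.7 and 14.4 are halved. The change-score loss is smallest, 33.8%, at ρ = 14.4/17.7 = 0.81. Below ρ = 17.7/(2 × 14.4) = 0.61, change is less precise even than follow-up alone.

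**Cost of estimating the slope.** Multiply the ANCOVA variance by 1 + 1/(N − 4) = 1 + 1/26 = 1.038. The change-score loss becomes 46.7%, 39.2% and 33.0%. Simulation of 20,000 trials of 15 + 15 gives 46.1%, 38.5% and 32.5%.

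**If the pre and post SDs were equal.** The ratio is (1 − ρ²)/(2(1 − ρ)) = (1 + ρ)/2, so the loss is 35%, 25% and 15%.

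**Power to exclude 10 points, complete data.** Noncentral t with 28 df and noncentrality 10/(SD·√(2/15)).

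| SDs | ρ | SD change | SD ANCOVA | Power, change | Power, ANCOVA |
|---|---|---|---|---|---|
| 8.85/7.2 | 0.3 | 9.59 | 6.87 | 79% | 97% |
| 8.85/7.2 | 0.5 | 8.15 | 6.24 | 90% | 99% |
| 8.85/7.2 | 0.7 | 6.40 | 5.14 | 98.5% | 99.9% |
| 17.7/14.4 | 0.5 | 16.30 | 12.47 | 37% | 56% |

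Charging ANCOVA for the slope and its degree of freedom moves 97% to 96.5% (first row) and 56% to 55% (last row). Follow-up alone with SD 7.2 has about 96%.

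**Chance imbalance.** The standard error of the baseline difference is √(2/15) = 0.365 SD, which is 3.2 points at SD 8.85 or 6.5 at SD 17.7. An imbalance b shifts the expected change contrast by b(ρ·s_post/s_pre − 1). At ρ = 0.5 the factor is 0.5 × 0.814 − 1 = −0.593. A one-standard-error imbalance therefore moves the contrast by about 1.9 points, or 3.8 with the unhalved SDs, against a difference of 10.

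**The case against.** The strongest case against has four parts.

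- **The loss is not a fact of the protocol.** It needs a correlation the document does not give and one cited study's SDs. This stands, and the range must carry both conditions.
- **On the protocol's own reading of the spreads, power is adequate.** With halved SDs and complete data, change-score power is about 79% at ρ = 0.3 and higher above that. This stands. A reader might infer from the 37% figure that the choice of metric leaves the trial underpowered, but that figure requires rejecting the protocol's 2×SD label, which is a different question.
- **Nothing rules out adjustment.** No test is named, ANCOVA on change is itself a parametric analysis of the stated metric with the same treatment estimate, and a condensed article may leave the model to an analysis plan. This stands in part: one cannot say the plan commits to a t-test or excludes covariates. But the article does fix the metric and the pre-test rule, and it describes two comparisons without adjustment in either. That is a choice open to improvement, not only a missing detail.
- **A valid analysis is being called biased.** A reader might infer that the change-score comparison is biased. Under randomisation it is not; the distortion is conditional on the imbalance that happens to occur.

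It is also tempting to say that a rank test can give no estimate in points. That is too strong, since a Hodges-Lehmann shift with an interval is available. The protocol does not say it would be reported.

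**Conclusion.** The point holds as a recommendation on efficiency and prespecification, not as an error that invalidates the trial. With the cited spread ratio, baseline adjustment beats the raw change score at every correlation. For ρ of 0.3 to 0.7 the loss is about 35–49%, or about 33–47% after the small-sample cost, falling to 15–35% if the SDs are equal. The other comparison described, of unadjusted follow-up scores, loses 9–49%. Under the protocol's halved SDs the practical gain is largest at low correlation (79% against 97% power at ρ = 0.3) and small at high correlation. It matters more if the true SDs are nearer 17.7 and 14.4, or if patients are lost. The normality switch is a weakness whichever correlation applies, because it leaves open which estimate will support the non-inferiority claim.

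**What to change.** Make the primary analysis one linear model of 24-month Kujala on treatment with preoperative Kujala as covariate, or take the same contrast from a repeated-measures model with baseline adjustment. Report the adjusted difference in points with its 95% CI and base the non-inferiority judgement on that interval. Remove the Shapiro-Wilk rule for choosing the test and keep a bootstrap or rank-based analysis as a sensitivity analysis. Use the same model for the secondary scores. Change from baseline can still be reported descriptively.

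The cost is one degree of freedom and a change of wording. No extra data, patients or visits are needed, and the model runs in the software the protocol names.

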## Background

Recurrent patellar instability incidence is 5.8/100,000 population, and reported recurrent dislocations are in the range of 15–80% [1, 2], with recurrence >50% after two dislocations [3]. Up to 55% of patients are unable to return to their pre-injury level of activity [4]. This can be particularly difficult to manage due to the multifactorial nature of patellar instability [3, 5], and a myriad of surgical options are described [6]. These include imbrication [7], repair by both open [8, 9], and arthroscopic techniques [10, 11] and reconstruction using a variety of graft options [9, 12–16].

The medial patellofemoral ligament (MPFL) is the most important restraint to lateral displacement of the patella from 0° to 30° of flexion, providing up to 60% of lateral patellofemoral stability [17]. MPFL insufficiency is present in 90% of acute, and 100% of recurrent, patellar dislocations [18]. Outcomes following MPFL reconstruction with autograft are reported as good to excellent, with increases in validated outcome measures for patellar instability, namely the Kujala score [3, 19–22].

Synthetic graft outcomes are also encouraging with studies reporting increases in Kujala outcome scores and patient-reported success rates of up to 94% [23–27]. One study reports the outcomes as being comparable to those of autograft reconstruction, with minimal need for revision intervention [25]. Stability is further enhanced when MPRL reconstruction is performed in combination with vastus medialis advancement compared to MPFL reconstruction alone [27].

Potential complications of MPFL reconstruction include re-dislocation, postoperative quadriceps dysfunction, adverse reaction to synthetic graft material, persistent pain and patellar fracture, but these risks are low and quoted as 5–10% [28–30]. Whilst multiple options are described, there is a paucity of clinical comparative studies. No study has compared autologous to synthetic graft reconstruction.

The objective of the current paper is to present a randomised controlled trial designed to investigate the difference, if any, between autologous semitendinosus synthetic graft MFPL reconstruction in patients with patellar instability.

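### Complications and revision are to be compared by chi-square with about one expected complication per arm, so the p value depends on which version is run; one named exact test with exact intervals should replace it

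*Protocol article*

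**What the plan says.** The section on statistical analysis and trial end points fixes the method for the two event outcomes: "the frequency of complications and all-reason revision will be recorded as a percentage and analysed by chi square analysis". It then sets one threshold: "For all tests, a *p* value <0.05 will be considered significant". It does not say whether the chi-square statistic carries a continuity correction. It names no exact test, no rule for small counts and no interval. The sentence about choosing parametric or non-parametric tests follows the Shapiro-Wilk normality test, so it concerns the scores and gives no fallback for a sparse two-by-two table.

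Two other sections supply the expected counts. The Background says of complications after this operation "but these risks are low and quoted as" 5–10%. For revision it gives no rate, only one earlier synthetic-graft study reporting good outcomes "with minimal need for revision intervention". The sample size section states "a total of 30 patients will be required – 15 in each treatment arm" and accepts attrition of up to 60% in each group.

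**The concern.** The chi-square test is a large-sample approximation, usually trusted when every expected cell count is about 5 or more. The protocol's own figures put the expected number of complications near one per arm. In that range the corrected and uncorrected statistics give very different p values, and the text does not say which will be used. The analysis is to be run by a study investigator, so a choice left open here could be made after the data are seen.

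Reporting adds to this. The Discussion expects the trial to inform patients about complication rates and to guide the choice of graft. If each arm is summarised by a percentage and a p value above 0.05, a reader of a trial framed as non-inferiority may conclude that the grafts are equally safe. Fifteen patients per arm cannot show that.

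**Working it through.** **Inputs.** Complication risk 5–10% (Background). 15 patients per arm and up to 60% attrition (Sample size). Significance at p < 0.05 (Statistical analysis); sidedness is not stated, and two-sided is assumed here.

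**The plan's own figure.** The document states no expected event count. Its total of 30 comes from the Kujala score and enters here only as a denominator. As a check, a two-sided normal approximation with d = 1.01, alpha 0.05 and 80% power gives n = 2 × (1.96 + 0.84)² / 1.01² ≈ 15.4, or 16 per arm. At 15 per arm the power is 0.790. The stated 15 is close enough to use.

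**Expected complications per arm.**
- 15 × 0.05 = 0.75; 15 × 0.10 = 1.5.
- With 60% attrition: 15 × 0.40 = 6 per arm, so 6 × 0.05 = 0.3 to 6 × 0.10 = 0.6.
- An expected count of 5 per arm needs a rate of 5/15 = 33%.

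**Chance that the usual condition is met.** With equal arms, the expected count in each event cell is half the total number of events, so at least 10 events in 30 patients are needed. At 5–10% the binomial chance of this is below 0.05%. The chance of no event in either arm, where chi-square is undefined, is 0.95³⁰ = 21% at 5% and 0.90³⁰ = 4% at 10%.

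**Worked table, 4 v 0 events of 15.**
- Uncorrected: 30 × (4×15 − 0×11)² / (15×15×4×26) = 108,000 / 23,400 = 4.62, p = 0.032.
- Continuity-corrected: 30 × (60 − 15)² / 23,400 = 2.60, p = 0.107.
- Fisher: 2 × C(15,4) / C(30,4) = 2 × 1,365 / 27,405 = 0.100.
- Unconditional exact (Barnard, pooled score, maximised over the common rate): 0.043.

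**Other tables, 15 v 15.**

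| Events | Uncorrected | Corrected | Fisher | Unconditional |
|---|---|---|---|---|
| 2 v 0 | 0.143 | 0.464 | 0.483 | 0.226 |
| 3 v 0 | 0.068 | 0.224 | 0.224 | 0.099 |
| 4 v 0 | 0.032 | 0.107 | 0.100 | 0.043 |
| 6 v 1 | 0.031 | 0.084 | 0.080 | 0.043 |

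**Long-run behaviour.** This comes from summing the product of two binomial probabilities over all tables with p < 0.05.
- Size at a common rate of 5% and 10%: uncorrected 0.5% and 2.5%; corrected 0.005% and 0.1%; Fisher 0.06% and 0.5%.
- Every table that Fisher rejects is also rejected by the uncorrected test, so their disagreement under no difference is the gap in size: 0.511 − 0.057 = 0.45% at 5%, and 2.459 − 0.545 = 1.9% at 10%.
- Power at 5% v 20%: uncorrected 19%, Fisher 8%. The same enumeration for the unconditional test gives about 19%.

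**What intervals would show.**
- Exact (Clopper-Pearson) upper 95% limit for 0 of 15: 1 − 0.025^(1/15) = 21.8%. For 1 of 15 the interval is 0.2% to 31.9%.
- Exact unconditional 95% interval for the risk difference, in percentage points: 1 v 1, about −26 to +26; 2 v 0, about −10 to +39; 4 v 0, about +2.5 to +52.5. The last excludes zero, in line with the unconditional p of 0.043.

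**The case against.** The strongest reply is that little goes wrong in practice. A reader might infer from the small expected counts that chi-square will produce too many false positives. It will not: at the quoted rates the uncorrected test is well below 5%, and Fisher is more conservative still. A reader might also infer that chi-square and exact tests routinely fall on opposite sides of 0.05. That is not supported either. The tables where uncorrected chi-square and Fisher split, 4 v 0 and 6 v 1, lie well above one event per arm, and with no true difference the two disagree in only about 0.5–2% of trials. In both tables the unconditional exact test sides with uncorrected chi-square. Moving to Fisher would therefore cost power to see a harm signal. All of this stands and limits the point.

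It can also be said that intervals and cautions on interpretation are often left to an analysis plan, and that the protocol nowhere claims equal safety. That is fair: the equal-safety reading is a risk in how results may be taken, not a statement in the document. But the test itself is not left open. The article names chi-square for these outcomes, and does so without saying which version.

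Two limits concern the inputs. No revision rate is given, so a count of about one or fewer revisions is an inference from the description of revision as minimal. And if 5–10% applied to each of the five listed complications separately, and these were independent, the chance of any complication would be 1 − 0.95⁵ = 22.6% to 1 − 0.90⁵ = 41.0%, or 3.4 to 6.1 patients per arm. Each single type would still be sparse.

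**Conclusion.** The point holds as a minor one. The protocol fixes a method whose usual condition has less than a 0.05% chance of being met at its own quoted rates, and it leaves open a choice of version that alone moves 4 v 0 events from 0.032 to 0.107. The documents do not support a claim of inflated type I error or of frequent conflict with exact tests. What remains is a p value that depends on the version run, and percentages from 15 patients per arm shown without their uncertainty.

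This rests on reading 5–10% as the overall complication risk, on 15 analysed per arm, and on two-sided tests at 0.05. These are secondary outcomes; the sample size and the primary Kujala comparison are unaffected.

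**What to change.** Replace the chi-square sentence with one that does three things:

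- Names a single exact test for complications and for all-reason revision, preferably an exact unconditional test with its statistic specified. "Fisher or unconditional" should not be left as alternatives, since they give 0.100 and 0.043 for the same 4 v 0 table.
- Makes the main safety result the event counts, with exact 95% intervals for each arm and an exact interval for the risk difference that matches the chosen test.
- States that a non-significant result will not be interpreted as equal safety.

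The cost is a sentence or two in the plan and slightly more analysis work, since the unconditional test and its interval may lie outside the standard menus of the planned software. The intervals will be wide, which is an honest picture of what 15 patients per arm can show. No change to design, recruitment or clinical conduct is needed.
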